### Ethics Approval

This study was approved by our local Ethics Committee (IRCCS Ca’ Granda Ospedale Maggiore Policlinico) on October 28, 2020 (protocol code 962_2020, 03/11/2020).

## Results

This project has been funded by Fondazione Cariplo under Award number 2020-1366, in June 2020. As of April 2022, we enrolled a total of 122 subjects, of which 94 have completed neuropsychological tests and web-based questionnaires; data analyses are currently completed in terms of preliminary results, and we expect results to be published by the end of 2022.

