**Results:**

As of April 2022, we enrolled a total of 122 participants, of which 94 have completed neuropsychological tests and web-based questionnaires.

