**Conclusions:**

Our study aims at testing the feasibility and preliminary efficacy of DigiCOVID, a remote telemedicine protocol for the improvement of psychological and psychiatric health in patients with COVID-19 and their relatives. To date, the approach used seems to be feasible and highly customizable to patients’ needs, and therefore, the DigiCOVID protocol might pave the way for future telepsychiatry-based interventions.

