## Methods

### Overall Design and Timeline

The study is conducted jointly by the units of pneumology, internal medicine, psychiatry, and the laboratory of brain injury and therapeutic strategies of the Istituto di Ricerche Farmacologiche Mario Negri. Before accessing DigiCOVID, participants are taken through the following steps: first, participants undergo an initial screening to ensure the main inclusion criteria are met. Then, 2 trained neuropsychologists remotely perform neuropsychological tests on patients via Zoom. The tests are aimed at assessing patients’ IQ through the Test di Intelligenza Breve (Italian for brief intelligence test) [23] and standard progressive Raven matrices [24]. Suicidality is assessed via the Columbia Suicide Severity Rating Scale [25]. Finally, participants complete a battery of web-based self-reports that include the following: the 12-item General Health Questionnaire [26], the Impact of Event Scale–Revised [27], the 7-item General Anxiety Disorder assessment [28], the Insomnia Severity Index [29], and the 9-item Patient Health Questionnaire [30]. After completing these assessments, participants are assigned to a trained psychotherapist who offers 8 teletherapy sessions carried out through Zoom.

This model is designed to be applied to patients with COVID-19 during hospitalization, after discharge, as well as during the remission and recovery phases. Similarly, this model is intended to be delivered to people who are dealing with the hospitalization or discharge after COVID-19 of a family member or have lost a family member due to COVID-19. A total of 8 remote, 50-minute, individual psychological sessions are offered weekly using secure videoconferencing software. The severity of the clinical conditions of patients with COVID-19 has largely influenced the sequencing of the intervention.

During all phases of the clinical work, suffering is contextualized both in the light of the recent traumatic experience (eg, bereavement, hospitalization in intensive care, and fear for one’s life or that of a relative) and in the light of historical ways of suffering, so that the patient is able to recognize the meaning of the symptoms experienced.

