#### Recruitment

As of April 2022, 122 participants have been referred to the study. Participation is voluntary, and an extended informed consent form is signed before any evaluation, assessment, or voice and video call. Consent forms are collected remotely for those who have been discharged and are currently in remission and in person for those hospitalized in a COVID-19 ward of either pneumology, internal medicine, or infectious disease departments.

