### Primary and Secondary Outcome Measures

#### Primary Outcome Measures

Efforts will be made to assess all participants who have completed the minimum required intervention activities. For DigiCOVID, the minimum required intervention activities include attending psychotherapy sessions at least 4 times. As the main goal of this project is to evaluate the feasibility, acceptability, and usability of DigiCOVID, we will conduct an analysis of the following primary outcome measures in all intention-to-treat (ITT) participants:

Assessment completion rate—based on our previous studies, we expect ≥80% of participants will complete the battery of web-based self-reports.Usability ratings obtained post DigiCOVID via a 7-point Likert scale questionnaire (ie, mean rating of all responses)—this is a brief and embedded poststudy questionnaire on program satisfaction, clarity, and perceived benefits. Participants will rate each sentence on the following 7-point Likert scale: 1=completely agree; 2=mostly agree; 3=somewhat agree; 4=undecided; 5=somewhat disagree; 6=mostly disagree; and 7=completely disagree. Based on our previous studies, we hypothesize exit survey ratings of at least ≥4.5 (SD 1.5) on the 7-point Likert scale items.Reported side effects (ie, raw score)—based on our previous findings, we expect 0 adverse events due to program use.Overall program completion rate—based on previous findings, we hypothesize full program completion in ≥70% study participants.

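### The ≥80% assessment-completion outcome names no time point and is measured only in participants with at least 4 sessions, so it cannot fail at baseline and omits early dropouts after treatment

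*Protocol article*

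**What the plan says.** Primary Outcome Measures lists assessment completion first among four feasibility outcomes: "we expect ≥80% of participants will complete the battery of web-based self-reports". The same section says the primary outcomes are analysed in the ITT participants. Data Analysis defines that population as those who attended at least 4 remote psychotherapy sessions.

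Overall Design and Timeline describes the self-report battery twice. It is completed before therapy, together with the neuropsychological tests, and "After completing these assessments, participants are assigned to a trained psychotherapist". It is then repeated at the end of the therapy cycle.

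Three places give a head count for April 2022. The abstract says "we enrolled a total of 122 participants, of which 94 have completed neuropsychological tests and web-based questionnaires". Results says "we enrolled a total of 122 subjects, of which 94 have completed neuropsychological tests and web-based questionnaires". Recruitment says "As of April 2022, 122 participants have been referred to the study".

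The abstract's Conclusions add an interim remark: "To date, the approach used seems to be feasible".

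**The concern.** The main goal of the study is to judge feasibility, acceptability and usability, and assessment completion is one of the four outcomes chosen for this. A benchmark of this kind is informative only if a poor result is possible and the people at risk of not completing are in the denominator. Here the time point is left open, and the population is defined by something that happens after the baseline battery and partway through therapy. The outcome can therefore be reported on either battery, and on each reading the denominator favours success.

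The reported counts add a second difficulty. Referral comes before consent and screening, and enrolment comes after them. One number carrying both labels leaves the denominator of any completion rate from these counts unclear.

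**Working it through.** The article prints no completion percentage, so there is no figure of its own to reproduce. The check has three steps.

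**1. What the benchmark measures under each reading**

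Inputs: the ≥80% benchmark and its population (Primary Outcome Measures), the ITT definition of at least 4 sessions (Data Analysis), and the order of assessments (Overall Design and Timeline).

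- *Baseline battery.* Attending 4 sessions requires a therapist, and a therapist is assigned after the baseline assessments. If the sequence is followed, everyone in the denominator has already completed the battery. The rate is n/n = 100%, apart from departures from the sequence, and a threshold of 80% cannot be missed.
- *Post-treatment battery.* Let d be the share of participants assigned to a therapist who stop before session 4, and r the post-treatment completion rate among those with at least 4 sessions. If early leavers do not complete the battery, the rate among all assigned is r × (1 − d). The documents give no value for d. As an assumption, let it run from 0 to 0.30; the upper end is the largest loss compatible with the article's ≥70% programme-completion benchmark, if that is read over all assigned. With r = 0.80:
  - d = 0: 0.80 × 1.00 = 80%
  - d = 0.30: 0.80 × 0.70 = 56%

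  The article's definition reports 80% in both cases.

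**2. The reported counts**

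Inputs: 94 and 122 (abstract and Results).

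- 94/122 = 77.0%, exact 95% confidence interval 68.6% to 84.2%.
- 0.80 × 122 = 97.6, so 98 completers would be needed. The count is 98 − 94 = 4 short.
- If the true rate were 80%, the probability of 94 or fewer out of 122 is 0.24 (two-sided exact p = 0.43).
- 94/0.80 = 117.5. With 94 completers the rate is 94/118 = 79.7% or 94/117 = 80.3%, so removing 122 − 117 = 5 people from the denominator moves it across the threshold.

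**3. Whether 94/122 is the benchmarked quantity**

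| | Benchmark | Reported count |
|---|---|---|
| Numerator | Self-report battery completed | Neuropsychological tests and questionnaires both completed |
| Denominator | Participants with at least 4 sessions | 122 people, called enrolled in two places and referred in a third |
| Time | Not stated | Not stated; pairing with the neuropsychological tests suggests baseline |

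Neither the numerator nor the denominator matches. The number with at least 4 sessions and the number completing the self-reports alone are not given, so the benchmarked rate cannot be computed from the article.

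**The case against.** A reader might infer something stronger: that the article's own data show 77% against a benchmark of 80%, and so contradict its statement that the approach seems feasible. The documents do not support this.

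- The 94 had to complete the neuropsychological tests as well, so 94 is only a lower bound for self-report completion.
- The 122 are not the population in which the benchmark is set.
- The Discussion says recruitment was still being completed, so some of the 28 (122 − 94) may not yet have reached assessment. Others may have been excluded at that stage, since low IQ on these tests and suicidal ideation are exclusion criteria assessed there.
- Even taken at face value, the shortfall is compatible with a true rate of 80%.
- The feasibility remark is hedged, and the Discussion presents feasibility as a hopeful prediction that awaits conclusive analyses.

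All of this stands. It rules out both a contradiction and an arithmetic error.

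It can also be said that a full participant flow belongs in the results report and that a status line in a protocol article need not supply one. That is fair, and it makes the enrolled/referred conflict, taken alone, a matter of wording.

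Neither argument reaches the definition of the outcome. The order of assessments, the benchmark and the population are all fixed in the article itself, and together they produce the problem whatever the interim counts turn out to mean. It is not a detail left to a fuller analysis plan.

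**Conclusion.** The assessment-completion outcome is badly fixed. On the baseline reading it is about 100% by construction and carries no information. On the post-treatment reading it is restricted to participants already retained to session 4. With 80% completion among those retained, the rate among all assigned could lie anywhere from 80% down to 56%, if between none and 30% leave before session 4 and early leavers do not complete the battery. The baseline conclusion assumes only that the described sequence is followed. The size of the post-treatment effect depends on an early dropout rate that the article does not give.

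Separately, the same 122 people are called enrolled in the abstract and Results and referred in Recruitment. The passages must be reconciled before any rate is formed from them. The 77.0% is correct arithmetic on the reported counts, but it is not a test of the ≥80% criterion and should not be printed as one. The interim impression of feasibility has therefore been neither confirmed nor refuted against this benchmark.

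**What to change.** 1. Define two rates: baseline battery completed among all eligible consented participants, and post-treatment battery completed among all participants assigned to a therapist, including those who stop before session 4.
2. State that the ≥80% criterion applies to the post-treatment battery, or state explicitly which of the two it applies to. Do not count baseline completion among treated participants as a success.
3. Use one label for the 122 in the abstract, Recruitment and Results. When rates are reported, give the counts referred, enrolled, assessed, assigned to a therapist and attending at least 4 sessions.
4. Add to the abstract's Conclusions that the impression of feasibility has not yet been tested against the benchmark.
5. Because Results says preliminary analyses are already complete, record when the definition was settled and that preliminary results were available by then.

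The cost is some rewording and a recount from the study's own records. The resulting completion rate may be less favourable than the one under the present definition.

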## Discussion

### Expected Outcomes

This paper describes the methodology adopted to remotely assess and promptly treat psychiatric symptoms in a sample of patients with COVID-19 and their first-degree relatives. This digital approach is showing its innovation potential by helping to manage the psychological burden caused by the pandemic in patients with COVID-19 and their relatives.

We expect, as a prediction of our hypotheses, that the DigiCOVID protocol will result in a feasible approach; such a claim is clearly a hopeful statement, yet it is based on the quick, efficient, and technological step procedure described earlier. In terms of descriptive statistics, we might observe slight differences in terms of symptoms between patients and relatives (ie, in the posttraumatic scale, which we expect to be higher in patients than in relatives). In conclusion, we also expect the DigiCOVID protocol to be effective for both patients and their relatives in diminishing psychological distress. Future directions might involve the standardization of the DigiCOVID protocol in COVID-19 wards, as part of a complete program for the treatment of patients with COVID-19 and participants who might not have the opportunity to move to see a professional if remote visits are not possible.

To date, we are completing the recruitment, and we are expecting future and conclusive analyses to determine the efficacy and effectiveness of the protocol.

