A multitude of digital approaches have been tentatively operationalized worldwide to meet clinical needs, with COVID-19 serving as a catalyst for a change in the way instruments are used daily in health care settings [17]. Telepsychiatry, an innovative approach that consists of remote consultations and evaluations for mental health symptoms, has become a reliable alternative to face-to-face assessments, thus adapting rather than succumbing to COVID-19 [18,19], and assisting those affected by the psychosocial consequences of the pandemic [20].

Aside from patients with COVID-19, the psychological aftermath of this pandemic to a similar degree interests those who have not contracted the virus but have clinical conditions to manage, have lost family members or peers, are unable to enjoy the physical presence of their families, and have been living in restricted conditions for months. This phenomenon is likely due to the general psychological impact of the pandemic event per se and the systemic modifications in family relationships, with high amounts of stress also in healthy relatives [21,22]. Incidence and prevalence of psychological distress have been skyrocketing beyond the possibilities of any mental health system to intervene with in-person services. This segment of the population has profound unmet clinical needs and increasingly requests access to psychiatric services.

In this paper, we aim to describe DigiCOVID, a digital mental health protocol designed to offer remote, personalized support to former or current patients with COVID-19 and their relatives. DigiCOVID includes psychotherapy sessions and psychiatric consultations depending on participants’ needs. An observational longitudinal study in patients with COVID-19 and their relatives is being conducted to investigate whether the intervention described above is feasible, usable, and acceptable for the target population. Outcome measures include engagement rates with psychotherapy sessions and psychiatric consultations, overall program completion rates, reported adverse effects, usability ratings, and clinician burden. The secondary objectives aim to (1) evaluate whether DigiCOVID induces changes in self-reports of anxiety, depression, insomnia, trauma, and quality of life and (2) determine whether DigiCOVID impacts patients with COVID-19 and their family members differently.

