This paper follows the SPIRIT guidelines for the trial’s publication, as suggested by the EQUATOR Network. The trial is registered on ClinicalTrials.gov (NCT05231018). Of note, the protocol has been registered as it was designed at the beginning of the project, that is, it did not include relatives but only patients. Given the high number of requests, and because the intervention is customizable to each patient’s clinical needs, we have decided to extend our intervention to relatives, thus explaining the differences between the registered protocol and this methodological paper. Regarding the gap between the registration and the trial start, the internal organization of our research unit does not require the registration of trials that do not involve drugs and placebos. Therefore, the trial has been registered on ClinicalTrials.gov to improve the recruitment process.

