#### Secondary Outcome Measures

The secondary outcome measures will be collected at baseline and immediately after the treatment for all participants. We designed DigiCOVID to improve mental well-being. Therefore, we will measure the impact of the intervention by looking at pre-post changes in the following outcome measures: the 12-item General Health Questionnaire [26] , the Impact of Event Scale–Revised [27], the 7-item General Anxiety Disorder scale [28], the Insomnia Severity Index [29], and the 9-item Patient Health Questionnaire [30]. We expected to observe a significant improvement across all these secondary outcome measures *P*< in both patients with COVID-19 and their family members. To verify these experimental hypotheses, we will conduct the analysis based on the preintervention (baseline) and postintervention data, using parametric and nonparametric statistical tests. The criterion for statistical significance is *P*<.05. Results with *P*<.1 will be described as trends.

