### Data Analysis

There are 3 a priori defined analysis populations, including a primary analysis population, a secondary analysis population designed to compare effect sizes in populations with no missing data, and a population who completed all study visits. The 3 populations are as follows:

ITT population: this is the a priori primary analysis population, defined as including all participants who attended at least 4 remote psychotherapy sessions.Intention-to-treat fully evaluable (ITT-FE) population: this is a secondary analysis population, defined as including all members of the ITT population who complete a postintervention visit. Note that a participant may complete a specific visit but have missing data for a test, in which case the participant is in the overall ITT-FE population but does not contribute data to the ITT-FE population for that visit (eg, the number of evaluable cases for a specific test on a specific visit may be smaller than the ITT-FE population for that visit because of missing data).Intention-to-treat completers (ITT-C) population: this is a secondary analysis population, defined as including all members of the ITT-FE population who complete all intervention sessions. Note that the ITT-C population is a strict subset of the ITT-FE population; a person who completes the treatment but does not complete the postintervention evaluation visit is not a member of the ITT-C population.

We also plan to perform different analyses in order to better describe the demographics of patients and relatives and to test whether there are significant differences in terms of response to our psychotherapy intervention.

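### A single-arm pre-post study cannot show that DigiCOVID causes improvement, or works differently in patients and relatives, but the secondary objectives and the Discussion claim both

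*Protocol article*

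**What the plan says.** The Introduction of the protocol article gives the design: "An observational longitudinal study in patients with COVID-19 and their relatives is being conducted". Under Overall Design and Timeline there is one route for everyone. After the assessments, "participants are assigned to a trained psychotherapist who offers 8 teletherapy sessions carried out through Zoom". The article mentions no randomisation, waiting list or untreated group.

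The Introduction words both secondary objectives causally. The first is to "evaluate whether DigiCOVID induces changes in self-reports of anxiety, depression, insomnia, trauma, and quality of life". The second is to "determine whether DigiCOVID impacts patients with COVID-19 and their family members differently".

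Secondary Outcome Measures names the estimator: "we will measure the impact of the intervention by looking at pre-post changes in the following outcome measures". The hypotheses are to be verified from baseline and post-treatment data, with significance at P<.05 and P<.1 described as a trend. Data Analysis adds analyses of patients and relatives to "test whether there are significant differences in terms of response to our psychotherapy intervention".

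Under Expected Outcomes the authors expect the program to be effective in both groups, and add that "we are expecting future and conclusive analyses to determine the efficacy and effectiveness of the protocol". The Conclusions of the Abstract claim less: feasibility and preliminary efficacy. The Limitations section discusses motivation and clinicians' adaptation to remote work. It does not mention the absent comparator, natural recovery or regression to the mean.

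**The concern.** Without an untreated comparison, the mean change from baseline to post-treatment mixes the effect of the program with everything else that moves the scores over the same weeks. In this population those other forces are likely to be strong. Inclusion criterion 2 requires a positive COVID-19 test at enrolment for the patient group. The Recruitment section says that some consent is taken on COVID-19 wards. The post-treatment battery follows a cycle of 8 weekly sessions, so physical recovery and discharge can both occur between the two measurements.

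The patient-relative contrast does not escape this. Both groups are treated, and their natural courses probably differ: patients recover from an illness, while relatives may be coping with a hospitalisation or a bereavement.

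The Strengths section links proof of efficacy to large-scale dissemination. A significant pre-post result read as an effect could therefore be used to support roll-out without evidence that the program did anything.

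**Working it through.** **1. Is there a figure to reproduce?** No. The article gives no sample size calculation, effect size, SD of change or patient-to-relative split for the secondary outcomes. The identification argument needs none of these. The numbers in steps 3 to 5 are illustrations under stated assumptions.

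**2. What each contrast estimates.**
- Objective 1: mean change = program effect + natural course and calendar trend + regression to the mean.
- Objective 2: patient change minus relative change = difference in program effects + difference in natural course and trend + difference in regression to the mean.

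Only the left-hand sides are observed. The terms on the right cannot be separated unless the untreated course is observed or assumed, in each group for objective 2.

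**3. Objective 1 with a program effect of zero.** Assumptions: pre-post correlation r = 0.6, n = 70 evaluable, two-sided 0.05 (the article does not state sidedness), paired t-test, natural improvement in baseline SD units with equal SDs at both times.
- SD of change = sqrt(2(1 − r)) = sqrt(0.8) = 0.894 SD.
- Noncentrality = (improvement / 0.894) × sqrt(70).

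| Natural improvement | Noncentrality | Probability of P<.05 |
|---|---|---|
| 0.2 SD | 1.87 | 0.454 |
| 0.3 SD | 2.81 | 0.790 |
| 0.5 SD | 4.68 | 0.996 |

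Range: at 0.3 SD and n = 70, the probability runs from 0.62 (r = 0.4) to about 0.98 (r = 0.8). At n = 94, the number assessed so far according to the Results, and r = 0.6, the three probabilities are 0.57, 0.90 and over 0.999. A larger sample makes the problem worse.

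**4. Regression to the mean alone.** If baseline scores average k SD above the level to which they tend to return, the expected fall is k(1 − r) SD. Divided by the SD of change, this is k(1 − r)/sqrt(2(1 − r)). Using a normal approximation with n = 94:
- k = 1: standardised change 0.45 (r = 0.6) to 0.32 (r = 0.8), giving P<.05 with probability 0.99 to 0.87.
- k = 0.5: 0.22 to 0.16, giving 0.58 to about 0.34.

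The inclusion criteria set no symptom threshold, so k depends on who volunteers, and it is unknown.

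**5. Objective 2 with the same program effect in both groups.** Let the natural courses differ by d, in SDs of change. The standard error is sqrt(1/n1 + 1/n2), by normal approximation, for an assumed total of 94.

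| d | 47 v 47 | 28 v 66 |
|---|---|---|
| 0.2 | 0.16 | 0.14 |
| 0.3 | 0.31 | 0.27 |
| 0.5 | 0.68 | 0.60 |

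Each entry is the probability of declaring a significant difference in response when the program works equally in both groups. The nominal rate is 0.05.

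**6. Wording side by side.** The Abstract claims preliminary efficacy. Expected Outcomes claims conclusive determination of efficacy and effectiveness. Both refer to the same study and cannot both stand.

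**The case against.** The main goal is feasibility, acceptability and usability, which one arm can address. Efficacy is secondary, the Abstract calls it preliminary, and the stated Objective already speaks of pre-post changes. The strongest sentence is a forward-looking remark in a Discussion, not a decision rule, and its reference to future analyses could mean later work. The probabilities above rest on assumed drift, correlation and sample size, and illustrate a limit common to all pre-post designs.

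Most of this stands as a limit on scope: the point concerns the secondary objectives and the conclusion only. It does not remove the point. The Discussion sentence begins with completing this study's recruitment, and Secondary Outcome Measures already equates pre-post change with impact. An unseen SAP cannot help, because no analysis recovers an untreated course that was never observed.

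Three stronger readings are tempting, but the document does not support them.
- **That the later addition of relatives causes the problem.** The article says openly that "we have decided to extend our intervention to relatives" because of many requests. This may add selection and calendar-time differences, but no enrolment dates are given. Objective 2 would be unidentified even if relatives had enrolled from the first day.
- **That family clustering distorts the standard errors by a known amount.** Relatives might share a family with an enrolled patient, but the article does not say that pairs were enrolled. Bereaved relatives may have no patient to pair with, so no figure can be given.
- **That pooling hides a feasibility failure among patients.** The article gives neither the split nor group completion rates, and nothing in it excludes reporting by group.

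**Conclusion.** The point holds for both secondary objectives, for the description of pre-post change as impact, and for the Expected Outcomes sentence. These are causal claims from a design that supports description only. That conclusion follows from the design and rests on no assumed number.

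The size does rest on assumptions. With no program effect, r = 0.6 and n = 70, modest natural improvement of 0.2 to 0.5 SD gives a significant result on each scale with probability from about 45% to over 99%. The true drift is unknown, so these figures show how easily significance can arise. They do not predict the trial's result, and they do not show that the program is ineffective.

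The conflict between the Abstract and the Discussion is a plain inconsistency. The feasibility, usability and completion outcomes are untouched. The change should be made, because it alters what the trial may conclude.

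**What to change.** 1. Reword secondary objective 1 as change in the self-report scales during the program, and objective 2 as a descriptive patient-relative difference in change. Carry the same wording into Secondary Outcome Measures, Data Analysis and Expected Outcomes.
2. State that P values for change are not evidence of efficacy.
3. Report mean change with 95% CI separately for patients and for relatives. Further modelling detail can be left to the SAP.
4. Reconcile the Abstract's Conclusions with Expected Outcomes by removing the claim of conclusive efficacy and effectiveness.
5. Add the missing comparator, natural recovery and regression to the mean to the Limitations. Mention the later extension to relatives there as a further source of non-comparability.

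This needs no new data and no change to conduct. The cost is a weaker claim. If a causal claim is wanted, it needs a concurrent comparison group, which means a different study.
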